### Internal pilot phase data

Number of eligible patients;Number of consenting patients;Number of patients declining participation;Assessment of the number of patients who attend or miss scheduled follow-up;Reasons for missed follow-up appointments;Barriers to timely scheduling of interventions and follow-up.

### Interventions

#### NPWT

Negative pressure dressings use an open-cell foam laid on top of the wound, which is then covered with an impermeable adhesive membrane. A sealed tube punctures the membrane to connect the dressing in-built pump, leading to the creation of a partial vacuum over the wound. The device is licensed to stay *in situ* and sealed for 5–7 days. In some cases, depending upon the treating surgeon’s normal practice and the volume of wound exudate, the wound may be redressed again on the ward. The postoperative day that the dressing was first removed will be recorded, as will the application of any subsequent NPWT dressings or dry dressings. For the purpose of this trial, NPWT device(s) may be used for up to 14 days after surgery.

#### Standard dressing

Standard dressing for an amputation wound comprises a non-adhesive layer applied directly to the wound, covered by a sealed dressing, supplemented with protective padding. Such standard dressings do not use negative pressure. The precise details of the materials used will be at the discretion of the treating surgeon as per their routine practice but the details of each dressing applied in the trial will be noted. The duration that each dry dressing is left *in situ* varies between surgeons, though the majority will leave the first dressing for a minimum of 48 hours and a maximum of 5 days. For the purpose of this trial, the type and duration of control dressing will be recorded, including the postoperative day the dressing was first removed.

Of note, it is some surgeons’ usual practice to use a drain in the amputation stump delivered out through a separate incision to protect against haematoma formation; the drain is usually ready for removal at 48–72 hours after surgery. There is a lack of high-quality evidence supporting drain use after major amputation; however, it a widespread practice. Achieving a durable seal for NPWT around a drain can be technically challenging, and a seal may be lost once the drain is removed; extra care should be taken to maintain a seal once the drain is removed. For the purpose of this study, surgeons should not alter their regular practice regarding drain use. The presence or absence of a wound drain will be recorded in the procedural data, allowing for potential subanalysis of the impact of drain use on outcomes.

### Schedule of events

#### Follow-up

At 1, 3, and 6 months, participants will be followed up in clinic where Wound-QoL, CoPaQ, and EQ-5D-5L quality of life questionnaires will be collected (*Fig. 1*). Details of late complications and any further surgical interventions will be recorded at these time points also. A window of +/− 2 weeks is permitted for each time point. These data will be uploaded onto the secure REDCap database. The number and timing of any subsequent follow-up appointments for clinical purposes will be at the discretion of the treating surgeon.

### Device assessment

The single-use NPWT device will be reviewed daily by the surgical team and issues with sealing and exudate will be recorded. The number of devices left *in situ* sealed appropriately for the recommended period (minimum 5 and maximum 7 days) will be noted. All episodes of resealing on the ward will be documented. Reasons for premature removal of the NPWT device will be recorded.

#### Wound assessment

The surgical incision will be reviewed by the clinical team as appropriate while the patient remains in hospital. All incidences of wound complications will be documented prospectively. The presence of SSI will be determined using the CDC criteria. The time taken in days from surgery to wound healing will be recorded. At 30 days, the surgical incision will be reviewed by a surgeon blinded to the initial wound management strategy and categorized as ‘healed’ or ‘not healed’.

### EQ-5D questionnaire

Quality of life will be evaluated by completion of the EQ-5D form at 3 and 6 months. These data will be further utilized to generate health economic data.

### Crossovers

Any crossovers between treatment groups shall be highlighted and reported in the final report. Participants’ follow-up data will continued to be recorded on an intention-to-treat basis, as such patients will continue to be analysed in the group they were originally randomized to whether they received the correct intervention or not. Reasons for protocol deviation will be documented in the site logs, for example NPWT device unavailable or unable to achieve seal despite multiple attempts or surgeon preference. Patients in the control group with unhealed wounds after the initial 14-day review period for whom the treating surgeon feels may benefit from application of a single-use NPWT device will be offered one.

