### Randomization

Following the consent process, eligible patients will be enrolled in the study through the online randomization system at the time of surgery in the operating theatre. Randomization will be on a one-to-one basis using a computer randomization program, with balanced allocation of patients across the two treatment groups, stratified by trial centre. All monitoring operating theatres can provide immediate internet access permitting the use of a secure 24-hour web-based randomization system to generate treatment allocation during surgery. Final eligibility will be confirmed by the treating surgeon at the end of the operative procedure before the wound dressing is applied, as a small subset of patients may be deemed clinically inappropriate for wound closure. A unique trial number will be assigned to each individual at the time of randomization. Patients will be randomized to one of two groups. There will be no sham intervention.

Group 1: single-use NPWT device applied to the closed skin incision after amputation.

Group 2: standard dry dressing applied to the closed skin incision after amputation.

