Use of randomization by stratification should ensure balance in the recruiting centre in both treatment groups. Whereas clustering effects are not expected to be important for this study, in reality the data may be hierarchical, with patients naturally clustered into groups by recruiting centre. This will be accounted for by generalizing the conventional linear (fixed-effects) regression approach to a mixed-effects logistic regression analysis. This model will be used to assess differences in wound complication rates between the study intervention groups, with results presented as odds ratios with associated 95% confidence intervals. The mixed-effects model will include a random effect to account for any heterogeneity in response due to the recruitment centre and fixed effects to adjust for vascular status. An identically structured and formulated mixed-effects linear regression model will be used to assess the effects of the interventions on secondary outcomes and EQ-5D-5L (at 1, 3, and 6 months) that, for the purposes of analysis, will be assumed to be approximately normally distributed. Other dichotomous outcome variables, such as complications related to the trial interventions, will be analysed in the same manner as the primary outcome. Temporal patterns of any complications will be presented graphically, and, if appropriate, a time-to-event analysis (Kaplan–Meier survival analysis) will be used to assess the overall risk and risk within individual classes of complications. All reported tests will be two-sided and considered to provide evidence for a significant difference if *P*-values are less than 0.05 (5% significance level. Results from this trial will also be compared with results from other trials and reported in accordance with CONSORT guidelines. Whereas there are a multiplicity of secondary outcomes, considering CONSORT guidelines and regulatory body preferences, the authors do not plan to adjust for type 1 errors due to the high risk of a corresponding increase in type 2 errors^22^.

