### Sample size

The data on the impact of prophylactic NPWT on wound complication following major amputation are limited. Retrospective cohort studies^6–10^ of wound complications with standard therapy after amputation reportedly range from 10 to 34%. In a recent meta-analysis^21^ of NPWT for major amputations, the pooled proportion of composite wound complications for patients using NPWT was 16%. For planning purposes, and based on the previously published range, it has been assumed that 25% of participants randomized to standard dressings will develop a wound complication. To investigate an absolute risk reduction of 10% with the use of NPWT (that is, a wound complication rate of 15%), with 90% power at the 5% significance level, a minimum of 331 patients will be required in each arm. To allow for losses to follow-up and withdrawals, 10% will be added to each arm. Therefore, the total projected sample size for the full trial is 728 patients.

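### Lack of an NPWT device is foreseen as a reason, found after randomisation, for not giving the allocated dressing, although stock could be checked before allocation is released

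*Protocol article*

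**What the plan says.** Under Randomization, patients are enrolled through an online system in theatre at the time of surgery, and the allocation is generated during the operation. The section also provides a last check: "Final eligibility will be confirmed by the treating surgeon at the end of the operative procedure before the wound dressing is applied". The reason it gives is that a few patients may turn out to be unsuitable for wound closure. Neither that section nor the inclusion and exclusion criteria mention device availability.

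Under Crossovers, patients are analysed in the arm to which they were randomised, whatever dressing they received. Reasons for protocol deviation go into the site logs, with the examples "for example NPWT device unavailable or unable to achieve seal despite multiple attempts or surgeon preference". The same section says that control patients with unhealed wounds after the 14-day review period may be offered a single-use NPWT device.

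Under Sample size, the control risk is set by "it has been assumed that 25% of participants randomized to standard dressings will develop a wound complication", and the NPWT risk is taken as 15%. The result is stated as "with 90% power at the 5% significance level, a minimum of 331 patients will be required in each arm". The inflation is described as "To allow for losses to follow-up and withdrawals, 10% will be added to each arm", giving 728 in total. Crossover is not mentioned there.

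**The concern.** The three example reasons differ in when they can be known. A seal that will not hold is discovered only once the allocated device is applied. An empty shelf is a fact before anyone opens the randomisation page. As the article is written, a site could randomise with no device to hand, apply a dry dressing to a patient allocated NPWT, and record a deviation.

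Lack of stock acts in one direction only, because dry dressings are always available. Each such patient adds control-type risk to the NPWT arm. Intention-to-treat is the right analysis and keeps the comparison fair, but it cannot restore contrast that was lost in theatre. A real benefit would look smaller, and the trial would have less power than planned, for a reason that is avoidable at almost no cost.

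**Working it through.** **Inputs.** From Sample size: control risk 0.25, NPWT risk 0.15, power 90%, 5% significance, 331 per arm, 10% added per arm. From Statistical analysis: "All reported tests will be two-sided". From Randomization: 1:1 allocation. The crossover fraction c is not in the documents and is assumed over a range.

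**Step 1: reproduce the plan's figure.** Two proportions, unpooled normal approximation:

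n = (1.960 + 1.2816)² × (0.25×0.75 + 0.15×0.85) / 0.10² = 10.507 × 0.315 / 0.01 = 330.98, so 331 per arm.

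331 × 1.10 = 364 per arm, and 2 × 364 = 728. Both stated figures reproduce. The whole margin of 33 per arm is assigned to losses and withdrawals.

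**Step 2: dilution.** If a fraction c of the NPWT arm receives the dry dressing and carries control risk, the NPWT-arm risk is

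p₂ = 0.15 + 0.10c, and the difference is d = 0.10(1 − c).

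Each 5 points of crossover therefore takes 0.5 percentage point off the difference.

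**Step 3: power.** With the pooled variance under the null hypothesis and p̄ the mean of 0.25 and p₂:

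power = Φ{ [d√n − 1.960√(2p̄(1−p̄))] / √(0.25×0.75 + p₂(1−p₂)) }

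Worked for c = 10% and n = 331: p₂ = 0.16, d = 0.09, p̄ = 0.205. The numerator is 0.09×18.193 − 1.960×0.5709 = 1.6374 − 1.1190 = 0.5184. The denominator is √(0.1875 + 0.1344) = 0.5674. The ratio is 0.914 and Φ(0.914) = 82.0%.

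| Assumed one-way crossover c | NPWT-arm risk | Power, 331 per arm | Power, 364 per arm (no losses) | n per arm for 90% power |
|---|---|---|---|---|
| 0 | 15.0% | 89.7% | 92.3% | 335 |
| 2% | 15.2% | 88.4% | 91.1% | 350 |
| 5% | 15.5% | 86.2% | 89.2% | 374 |
| 10% | 16.0% | 82.0% | 85.4% | 421 |
| 15% | 16.5% | 77.1% | 80.9% | 477 |

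The first row gives 335 rather than 331 because this formula pools the variance. The difference is one of method and not an error in the plan.

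**Step 4: what the fractions mean.** Of 331 NPWT patients, 2% is about 7 (0.02×331 = 6.6), 5% about 17 (16.6) and 10% about 33 (33.1). The fraction c covers every cause of receiving the dry dressing, including seal failure. Missing devices would be only part of it.

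**The case against.** The strongest reply is that the Crossovers section is a recording rule. It names these events as protocol deviations and has them logged, and crossovers are to be reported. A reader might infer that the plan accepts or permits them, but the text does not say so. A log must be able to record such events even at a well-supplied site. That stands: the plan foresees the problem and records it, but describes nothing to prevent it.

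A reader might also treat surgeon preference in the same way, as a one-way and avoidable loss. The documents do not support this. Preference can move patients in either direction. It may form only when the stump is seen at closure or once the allocation is known, so a check beforehand would remove only part of it. Nothing in the article shows that overrides follow wound risk. The after-day-14 offer to control patients also shows that crossover in this trial does not run only from NPWT to dry.

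It can further be said that this is a condensed article, that form fields and stock arrangements may be in the full protocol, and that oversight exists through audit, six-monthly Steering Committee review and the power to suspend for poor compliance. This stands in part. Silence does not prove that no check is made. However, the article describes the theatre procedure in some detail, gives one reason for the last check, and itself expects missing devices to come up as a deviation. Audit finds such events afterwards and cannot undo them.

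The appeal to pragmatic design carries little weight for stock. Leaving dressing management to usual practice is a design choice, whereas randomising to a device that is not there tells us nothing about whether the device works.

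**Conclusion.** The point holds for device availability and is minor. The described procedure leaves room to randomise when the NPWT arm cannot be delivered. The resulting non-adherence runs one way, dilutes the intention-to-treat contrast and is not covered by the sample-size inflation.

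The size depends on an assumed rate. At 331 per arm, power is about 88% at 2% one-way crossover from all causes, 86% at 5% and 82% at 10%. If nobody were lost and all 364 per arm were analysed, 5% crossover would still leave about 89%. The figures assume that the planning risks of 25% and 15% are correct and that crossed-over patients carry the full control risk.

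A reader might go further and conclude that the sample size is wrong or that the 90% power is already lost. Neither follows: 331 and 728 reproduce, and no document gives a crossover rate. Keeping these patients in their randomised arm is also correct and should not change.

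**What to change.** In Randomization, add one mandatory item to the web form, answered before allocation is released: an NPWT device for this patient is physically in theatre. If the answer is no, do not randomise, and enter the reason on the screening log already described under Informed consent of the inpatient. Because the allocation is unknown at that moment, such exclusions cannot bias one arm against the other.

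A second item, that the operating surgeon will apply either dressing, is reasonable but secondary. It would screen out surgeons who are already unwilling. It would not stop preferences formed after allocation, and it could keep out some stumps that the surgeon judges high risk, which narrows a deliberately pragmatic population.

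Leave the Crossovers section logging whatever deviations remain. The cost is a tick box and a few eligible patients not randomised when no device is to hand.

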### Withdrawals during follow-up

Participants may decide to discontinue the participation in the trial at any time without prejudice. Such a decision to withdraw will not affect the standard of care the patient receives. They may either withdraw from completing any further questionnaires but allow the research team to collect relevant hospital data in relation to postoperative complications, which are recorded as part of normal standard of care, or they may withdraw completely from the study. Data obtained up into the point of withdrawal will be included in the final analysis; thereafter, no further data will be collected for the participant. Patients will be followed up as per standard of care should they withdraw. The principal investigator may withdraw an individual from the trial should they be subject to an adverse event whereby it is in the patient’s best interest to be withdrawn or should they meet any of the exclusion criteria.

### Loss to follow-up

Prior to consent, participants will be educated as to the importance and timing of the follow-up protocol. Should follow-up appointments be missed, investigators will endeavour to contact patients by phone or via community liaisons to ensure timely follow-up within the trial protocol. All losses to follow-up and its cause shall be recorded and reported in any trial data.

### Protocol violations

Patients may be excluded in the phase after randomization if it is established they were unable to adhere to trial procedures, for example completing questionnaires. Patients can also be withdrawn at the principal investigator’s discretion if it is in the best interests of the patient.

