## Statistical considerations

### Statistical analysis

Once randomization and intervention is complete, patient outcomes will be assessed using an intention-to-treat analysis. All losses to follow-up at any time point will be recorded and reported. A blinded biomedical statistician will conduct all analyses independently of the data collection team. Statistical analysis will be conducted using SPSS^TM^ Version 29 (IBM Corp, Aramonk, New York, United States). Baseline data will be summarized to check comparability between treatment arms. The main analysis will investigate differences in the primary outcome measure, the proportion of patients with any wound complication at 30 days after major amputation.

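### The rules for excluding and withdrawing patients after randomisation conflict with the promised intention-to-treat analysis, so that analysis is not guaranteed

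*Protocol article*

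**What the plan says.** All references are to the protocol article.

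- **Analysis principle.** Under Statistical analysis, "patient outcomes will be assessed using an intention-to-treat analysis". Under Crossovers, "patients will continue to be analysed in the group they were originally randomized to whether they received the correct intervention or not".
- **Exclusion after randomisation.** Under Protocol violations: "Patients may be excluded in the phase after randomization if it is established they were unable to adhere to trial procedures". The only example given is questionnaire completion.
- **Withdrawal by the investigator.** Under Withdrawals during follow-up: "The principal investigator may withdraw an individual from the trial should they be subject to an adverse event", on condition that this serves the patient's best interest; meeting an exclusion criterion is a second ground. Protocol violations adds a general discretion: "Patients can also be withdrawn at the principal investigator’s discretion if it is in the best interests of the patient".
- **Data after withdrawal.** Data already obtained stay in the final analysis, but "thereafter, no further data will be collected for the participant". Participants who themselves withdraw may instead stop only the questionnaires and "allow the research team to collect relevant hospital data in relation to postoperative complications". No such option is stated for a withdrawal initiated by the investigator.
- **Blinding.** Under Randomization, "There will be no sham intervention". The 30-day wound review and the statistician are blinded.

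**The concern.** An intention-to-treat comparison is protected by randomisation only if the analysis set is fixed at randomisation and outcomes are sought for everyone in it. A rule that permits later exclusion for not managing trial procedures removes the first condition. A rule that ends data collection when the investigator withdraws a patient removes the second.

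The questionnaire example is hard to justify. The primary outcome is any wound complication at 30 days, diagnosed by the treating team and confirmed from report forms. A patient who completes no questionnaire can still contribute it in full.

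Both sets of rules operate after allocation, in a trial where the dressing can be seen. If the patients removed differ between arms in their risk of wound complication, the estimated odds ratio is biased. The blinded 30-day review and the blinded statistician cannot recover patients who have already left.

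**Working it through.** **1. The plan's own sample size.** Inputs from Sample size: 25% against 15%, 90% power, 5% significance; tests are two-sided (Statistical analysis). With the unpooled two-proportion formula:

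n = (z₀.₉₇₅ + z₀.₉₀)² × (0.25×0.75 + 0.15×0.85) / 0.10² = 330.98, so 331 per arm.

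Total with 10% added: 331 × 1.1 × 2 = 728.2, so 728. Both figures reproduce.

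**2. What the 10% allowance covers.** With 364 per arm and 10% lost, 364 × 0.9 = 327.6 per arm remain, and power is about 89% (pooled formula). The allowance makes up numbers. It does nothing about who is lost.

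**3. What each rule can cost.**

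| Rule | Data kept | Data that can be lost |
|---|---|---|
| Exclusion for inability to adhere | Not stated whether exclusion is from participation or from analysis | If from analysis: the patient's whole contribution, primary outcome included |
| Investigator withdrawal before day 30 | Everything recorded up to that day | The primary outcome, if no complication has yet occurred; all later safety and follow-up data |
| Investigator withdrawal after day 30 | The primary outcome | Later safety data and the remaining 3- and 6-month outcomes |

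The primary safety outcome includes reintervention at any time, so later follow-up matters for safety too.

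**4. Illustration of selective exclusion from the analysis.** The protocol gives no exclusion rate and no risk for those excluded, so everything here except 25% and 331 is assumed. There is no true effect (25% in both arms), 331 per arm, and a fraction f of the NPWT arm only is removed, with complication rate r.

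Observed NPWT rate = (0.25 − f×r) / (1 − f)

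| f | r | Observed NPWT rate | Spurious benefit |
|---|---|---|---|
| 5% (about 17 patients) | 40% | 0.230/0.95 = 24.2% | 0.8 points |
| 5% | 60% | 0.220/0.95 = 23.2% | 1.8 points |
| 10% (about 33 patients) | 40% | 0.210/0.90 = 23.3% | 1.7 points |
| 10% | 60% | 0.190/0.90 = 21.1% | 3.9 points |
| any | 25% | 25.0% | 0 |

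By normal approximation, with 331 per arm less the exclusions, the chance of a false finding in favour of NPWT rises from the nominal 2.5% to about 4–8% (5% excluded) or 7–21% (10% excluded).

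**5. The other directions.** If the same fraction with the same risk is removed from both arms, both observed rates fall equally and, with no true effect, the spurious difference is zero. If the exclusions fall in the control arm only, the same arithmetic gives a spurious harm of the same size.

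**The case against.** The strongest defence is that the protocol states its analysis rule directly, twice, and that the exclusion sentence does not say what patients are excluded from. It may mean further participation, with the data kept in the analysis. The wording is discretionary, and data up to withdrawal are expressly retained. This stands to the extent that intention to treat cannot be called abandoned, only unsecured. Even on the mild reading, though, follow-up may stop for patients who have not withdrawn consent.

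Four stronger readings are tempting, and the protocol does not support them:

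- **That harm from the device is concealed.** An adverse event that prompts withdrawal precedes it, so it is already recorded, and the safety section says adverse events will be reported. If the event is itself a wound complication, the primary outcome has been captured. Only later data are at risk.
- **That only the NPWT arm is exposed.** Problems with the device, such as unavailability or failure to seal, are treated under Crossovers as deviations, with the patient kept as randomised. The one example of non-adherence, questionnaires, applies to both arms on the same schedule.
- **That the exclusion rule flatly contradicts the withdrawal section.** One gives the participant a choice; the other gives the trial a discretion. They can coexist, if awkwardly.
- **That those removed would be the frailest patients, chosen by staff who know the arm.** This is plausible, but the protocol describes neither who would be removed nor who decides on exclusion.

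It is also fair to say that the no-further-data sentence precedes the text on investigator withdrawal and is not expressly applied to it. Applying it there is the natural reading, since nothing else is provided, but it is a reading.

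**Conclusion.** The point holds in a limited form. The exclusion sentence conflicts with the as-randomised analysis promised elsewhere and serves no purpose for a primary outcome that needs no questionnaire. The withdrawal rules, read naturally, can end outcome collection for patients who did not ask for that. Intention to treat is therefore not guaranteed, and with visible dressings the loss could be selective.

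The size and direction of any bias cannot be determined from the protocol. The 0.8 to 3.9 points above, against a planned difference of 10 points, are a one-sided illustration and not an estimate. They require exclusions in one arm only, 5–10% of that arm removed, a 40–60% complication rate among those removed, and their events dropped entirely from the analysis. That last condition fits exclusion from the analysis set; it does not fit withdrawal with earlier data retained. With no true effect, balanced exclusions or exclusions unrelated to outcome give no bias.

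**What to change.** - **Protocol violations:** delete the sentence allowing exclusion after randomisation. State that every randomised patient stays in the primary analysis in the allocated arm, that missed questionnaires mean missing questionnaire data and nothing more, and that patients later found ineligible are kept in the analysis and listed.
- **Withdrawals during follow-up, and the discretion under Protocol violations:** state that withdrawal by the investigator ends trial procedures but not the collection of wound and safety outcomes from routine hospital records, unless the patient withdraws consent to this.

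When a patient's treatment should be stopped remains a matter for the investigators and is not addressed here.

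The cost is a few sentences of amendment. The protocol already describes postoperative complications as recorded in standard care, and the sample size stays at 728. Outcomes not collected at the time may not be recoverable later.
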